### Severe maternal adverse events related to tranexamic acid

Caution is necessary before recommending the use of this drug in routine practice for prevention or treatment of PPH, in view of the number of eligible women who would be eligible to receive it in both cases: not only is the evidence supporting its efficacy still insufficient, but also and especially the number of venous and arterial thrombotic events might increase after its administration. Consequently, until now, no authorities or learned societies have recommended the administration of TXA to prevent PPH, after either vaginal or cesarean delivery.

Because TXA inhibits fibrinolysis, it carries a potential risk of thrombosis, especially in patients with a previous history of thrombosis and in pregnant women. Nevertheless, the systematic review of randomized controlled trials of elective surgical patients cited above (129 randomized controlled trials including 10 488 randomized participants, 5484 of them allocated to TXA) showed no significant increases in the incidence of myocardial infarction, stroke, deep vein thrombosis, or pulmonary embolism [20]. Moreover, the CRASH-2 trial of TXA in bleeding trauma patients showed a statistically significant reduction in global mortality with no increase in thromboembolic events [21]. Nevertheless, as thromboembolic events are relatively rare, these trials do not resolve the uncertainties about this risk because most of these trials lacked the statistical power to detect clinically important increases in risk. In particular, five cases of acute renal failure due to thrombosis-induced cortical necrosis following TXA administration have been described [43–47].

The evidence available for assessing the safety of TXA use in parturients for prevention of PPH is even more limited than for nonpregnant patients, given the limited number of such women thus far enrolled in TXA trials and the expected incidence of these adverse events. It is well known that the risk of venous thromboembolism increases during normal pregnancy and especially during the first 6 weeks postpartum [48]. It is nonetheless important to underline that no significant increase in the incidence of thrombotic events related to TXA has been observed in any trials of TXA among pregnant women (*n* = 2228), including RCTs, observational nonrandomized studies and case series [49].

In conclusion, TXA appears to be a promising drug for the prevention of PPH, but the results currently available are too limited to justify its widespread use. Given the current uncertainty regarding both its efficacy and its adverse effects in parturient women, we propose to perform an adequately powered, multicenter, randomized, placebo-controlled trial to determine the impact of systematic TXA administration after vaginal delivery on PPH incidence. If TXA is effective, its routine use should reduce the incidence of PPH among women with vaginal deliveries. If TXA is shown to be ineffective, this will prevent the diffusion of an ineffective medication associated with potential adverse effects in routine practice.

The hypothesis is that a low dose of TXA (1 g) after vaginal delivery, administered in the 2 min after the child’s delivery and after prophylactic oxytocin administration, reduces both blood loss and the incidence of PPH and its complications.

### Objectives

The aim of this study is to compare the effect of a low dose of TXA (1 g) after vaginal delivery in the 2 min after the child’s delivery and after prophylactic oxytocin administration, versus placebo with prophylactic oxytocin in a multicenter randomized, double-blind, placebo-controlled trial.

The specific objectives are as follows:To assess the impact of TXA (1 g) after vaginal delivery on postpartum blood loss■ Primary outcome➢Incidence of PPH, defined by blood loss ≥ 500 mL, measured with a graduated collector bag■ Secondary outcomes➢Other outcome measures describing postpartum blood loss, such as mean measured total postpartum blood loss, incidence of severe PPH, defined by blood loss ≥ 1000 mL, proportion of women requiring supplementary uterotonic agent, transfusion, arterial embolization, or emergency surgery for PPH, and mean peripartum change in hemoglobin and hematocritTo assess the potential adverse effects of TXA (1 g) after vaginal delivery:■ The hemodynamic parameters, gastrointestinal side effects, renal, hepatic and coagulation function, venous or arterial thrombosis within 3 months following delivery.To assess women’s satisfaction and psychological status at D60

## Methods and design

### Recruitment and allocation

#### Inclusion criteria

Age ≥ 18 yearsPlanned vaginal deliveryTerm ≥ 35 weeks of gestationSingleton pregnancyInformed consent form signed

#### Exclusion criteria

History of venous (deep vein thrombosis and/or pulmonary embolism) or arterial (angina pectoris, myocardial infarction, stroke) thrombosisHistory of epilepsy or seizureAny known cardiovascular, renal, or liver disordersAutoimmune diseaseSickle cell diseaseSevere hemorrhagic diseasePlacenta previaAbnormally invasive placenta (placenta accreta/increta/percreta)Abruptio placentaeEclampsia, HELLP syndromeMultiple pregnancyIn utero fetal deathAdministration of low-molecular-weight heparin or antiplatelet agents during the week before deliveryPoor understanding of the French language

Individual information on the trial will be provided to women in late pregnancy by obstetricians and midwives during prenatal visits or by anesthetists during the systematic anesthesia visit, or both. This information will be repeated when the women arrive in the delivery room; each woman will then confirm her participation and provide informed written consent before delivery, when, in the investigator’s opinion once she has reached at least 4 cm of cervical dilatation, she is likely to have a vaginal delivery.

The randomization will be centralized and stratified by center and balanced in blocks of variable sizes. Once a woman has been included, through the filing of an electronic case report directly by internet (Clinsight software), she will retain her randomization number (if it has been assigned to her) even if she withdraws from the study or refuses randomization afterwards.

Women will be randomized to receive either 1 g of TXA (Sanofi Aventis, Paris, France; Marketing authorization number: 3400931157618 [1974, RCP rév 02.04.2010]) or placebo (normal saline, Fresenius Kabi, Sèvres, France; Marketing authorization number: 34009415 73941). The Angers Clinical Research Unit will create the randomization list for allocations to the TXA and control groups. This list will be transmitted to the pharmacy department of CHU Angers, which belongs to the PPRIGO hospital pharmacists’ consortium (Production Pharmaceutique pour la Recherche Institutionnelle du Grand Ouest). The blinded products will be prepared by the Angers CHU pharmacy according to GMP for hospital pharmacies (BPP 2007), which will provide numbered and labeled boxes, each containing a 10-mL vial of the study drug (1 g of TXA or placebo according to the randomization number). All boxes and vials will be identically labeled, with the study number being the only differentiating feature between different drug packs. This will ensure the woman’s safety and the blinding of all participants, including obstetric staff.

### Intervention

The intervention will be the intravenous administration of a 10-mL blinded vial of the study drug (either 1 g of TXA or placebo, according to the randomization group), slowly (over 30–60 sec), in the 2 min after birth and the routine prophylactic oxytocin, and after the cord has been clamped, all generally by the midwife (but sometimes by the anesthesiologist or obstetrician, depending on availability).

Except for the content of the study drug vial, all aspects of management of the third stage will be identical in both arms:Routine prophylactic intravenous injection of 5 IU oxytocin at delivery of the anterior shoulder or within 2 min of birth, as recommended in the national clinical practice guidelines issued by the French College of Gynecologists and Obstetricians [50].Placement of a graduated (100 mL graduation) collector bag just after birth, left in place for at least 15 min and then until the birth attendant judges that bleeding has stopped. When a woman is included in the trial, a bag will be prepared and ready to be put in place as soon as the baby is born and placed on the mother’s belly; if needed, a second staff person will be present to help in managing both the baby and the bag. This will make it possible to collect and measure vaginal blood loss objectively during the immediate postpartum [14].Manual removal of the placenta at 30 min after birth if not expelled, in the absence of bleeding.Rapid suturing of the episiotomy, in accordance with good clinical practices.Systematic use of uterotonic drugs after the third stage of labor is not recommended.Controlled cord traction (CCT) will be left to the discretion of the practitioner since its use in the management of placental expulsion has been shown to have no significant effect on the incidence of PPH or other markers of postpartum blood loss [14].

If PPH occurs, standardized management will be provided according to the department’s protocol. In particular, the use of TXA for the treatment of PPH will be allowed and left to the discretion of the practitioner, according to the department’s protocol.

Before inclusions begin, a meeting will be organized in each maternity unit to verify the attendants’ agreement to and understanding of the protocol and their ease in practicing the relevant procedures.

### Outcome measures

#### Primary outcome measure

The primary outcome of the trial is the incidence of PPH, defined by blood loss ≥ 500 mL, measured with a graduated collector bag. The term “measured” implies an objective determination of the blood volume lost, in contrast to a simple visual estimate, which has been shown unreliable in several studies [14, 51–55].

The systematic use of a graduated collector bag for blood, placed under the woman’s buttocks just after delivery of the child, will allow an objective measurement of the blood lost through the vagina in the immediate postpartum period.

The practical feasibility of the use of such a bag was shown in the TRACOR trial [14]. This bag shall be left in place for at least 15 min and afterwards until the birth attendant is no longer concerned about blood loss, and judges that the woman’s condition allows her to stretch out. This criterion will be measured during the immediate postpartum surveillance in the delivery room, in both groups.

#### Secondary outcomes

Secondary outcome measures describing postpartum blood loss

#### Clinical

mean measured blood loss at 15 min after birth (the collector bag must be left in place at least 15 min to have one measure of blood loss at the same time point for all women)mean measured total postpartum blood loss (at bag removal)incidence of severe PPH, defined by measured blood loss ≥ 1000 mL.proportion of women requiring supplementary uterotonic treatment, including sulprostoneincidence of postpartum transfusion (until discharge)incidence of arterial embolization and emergency surgery for PPH.

#### Laboratory

mean change in peripartum hemoglobin (difference between Hb before delivery and at D2)mean change in peripartum hematocrit (difference between Ht before delivery and on D2).

For both indicators, the pre-delivery reference examination will be the last routine blood count in the last trimester of the pregnancy. A blood sample will be taken from all women included in the trial on the second day postpartum for the measurement of peripartum Hb and Ht and the calculation of the change in these two indicators. If no blood sample is available from D2, measurement of postpartum Hb and Ht will be assessed from a D3 blood sample, if available. If no blood sample is available from D2 or D3, measurement of postpartum Hb and Ht will be assessed from a D1 blood sample, if available.The occurrence of potential adverse effects of TXA:

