### Statistical analysis

Data analysis and reporting will follow the CONSORT guidelines for randomized controlled trials and will be conducted with the trial statistician and researchers blinded to group status. The two groups will be compared for women’s demographic characteristics and standard risk factors for PPH. Then we will seek, in an intention-to-treat analysis, the existence of a “TXA effect”, that is, a difference between the two groups for the primary outcome measure and the secondary outcome measures. For secondary outcomes that are available for women who had a cesarean delivery after randomization (percentage of women requiring supplementary uterotonic agents, mean change in peripartum hemoglobin, mean change in peripartum hematocrit, incidence of postpartum transfusion, arterial embolization, and emergency surgery), a secondary analysis will be conducted that includes these women. The comparisons will use nonparametric statistical tests when required by the constraints of population size or distributions. Comparisons of the categorical variables will use chi2 and Fisher exact tests, as appropriate. We will use analysis of variance and Kruskal and Wallis’s nonparametric test for the continuous variables. Effects will be measured as relative risks, with their 95 % confidence intervals.

The analysis plan includes an intermediate statistical analysis when half of the planned women have been included to ensure there is no significant difference in the adverse events between the two groups.

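### Hemoglobin and hematocrit are compared as raw changes without adjusting for the pre-delivery value already collected or for center: unbiased, but less precise than it could be

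*Protocol article*

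**What the plan says.** Under Secondary outcomes, Laboratory, the protocol article lists "mean change in peripartum hemoglobin (difference between Hb before delivery and at D2" and "mean change in peripartum hematocrit (difference between Ht before delivery and on D2". The baseline for both is fixed there: "the pre-delivery reference examination will be the last routine blood count in the last trimester of the pregnancy". For the later value, "A blood sample will be taken from all women included in the trial on the second day postpartum", with a D3 and then a D1 sample as fallback.

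Under Statistical analysis, the method is: "We will use analysis of variance and Kruskal and Wallis’s nonparametric test for the continuous variables". Nonparametric tests are reserved for cases where group size or distribution calls for them. The section closes its account of methods with "Effects will be measured as relative risks, with their 95 % confidence intervals". It mentions no covariate.

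Under Recruitment and allocation: "The randomization will be centralized and stratified by center and balanced in blocks of variable sizes".

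**The concern.** Each woman's change needs her pre-delivery value, so the trial holds a baseline measurement for every woman who contributes to these outcomes. Subtracting it fixes its coefficient at 1. Regressing the D2 value on it lets the data choose the coefficient, and in a large randomized trial that cannot do worse. The baseline is a routine count from some point in the last trimester. The interval to delivery is not stated, but a longer one would tend to weaken the correlation with D2 and so increase what subtraction loses.

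What is at stake is the width of the confidence interval on two markers of blood loss that do not depend on reading the collector bag. They are also the only continuous blood-loss outcomes that Statistical analysis lists as available for women who had a cesarean after randomization.

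**Working it through.** **The plan's own figure.** The protocol gives no SD, correlation or power for hemoglobin or hematocrit. Its only sample size is for the primary outcome (Sample size section: 10 % against 7 %, two-sided 0.05, power 0.90). With the pooled-variance formula and no continuity correction,

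n = [1.960·√(2·0.085·0.915) + 1.2816·√(0.10·0.90 + 0.07·0.93)]² / 0.03² = 1814 per arm,

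which matches the protocol. It serves below only as the number of women per arm.

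**Precision.** Let r be the correlation of the pre-delivery and D2 values, and k the SD at D2 divided by the SD before delivery. Relative to the D2 variance,

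- raw change: (1 + k² − 2rk) / k²
- ANCOVA: 1 − r²
- ratio ANCOVA/change: k²(1 − r²) / (1 + k² − 2rk)

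The denominator minus the numerator is (1 − rk)², so the ratio never exceeds 1. It equals 1 only when rk = 1, that is, when the slope of D2 on baseline is exactly 1. With k = 1 the ratio is (1 + r)/2.

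Neither r nor k is in the document. Over an assumed range:

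| r | k = 1.0 | k = 1.2 |
|---|---|---|
| 0.3 | 0.65 | 0.76 |
| 0.5 | 0.75 | 0.87 |
| 0.7 | 0.85 | 0.97 |

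For example, with k = 1.2 and r = 0.7: 1.44 × 0.51 / (2.44 − 1.68) = 0.7344 / 0.76 = 0.97. The variance saved is therefore about 3 % to 35 %. With equal SDs the confidence interval narrows by 1 − √0.65 = 19 %, 1 − √0.75 = 13 % and 1 − √0.85 = 8 %.

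Simulated trials with 1814 women per arm and equal SDs gave ratios of 0.650, 0.740 and 0.831 at r = 0.3, 0.5 and 0.7. Both estimators were centered on the true difference.

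**In hemoglobin units.** The Background reports day-after-delivery SDs of 1.4 and 0.9 g/dL in an earlier vaginal-delivery trial. Pooled, that is √((1.96 + 0.81)/2) = 1.18. Taking this SD at both times, r = 0.5 and 1814 per arm:

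- raw change: SE = √(2 × 1.18² × 1.00 / 1814) = 0.039 g/dL; difference detectable with 90 % power = 3.24 × SE = 0.127 g/dL
- ANCOVA: SE = √(2 × 1.18² × 0.75 / 1814) = 0.034 g/dL; detectable difference = 0.110 g/dL

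Power for an illustrative difference of 0.1 g/dL rises from 72 % to 84 %.

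**Center.** The document gives no between-center variation in hemoglobin, so no gain is computed for including center. It belongs in the model because randomization is stratified by it.

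**The case against.** The strongest reply is that nothing here is wrong. In a randomized trial the comparison of mean changes is valid, and adjustment of a secondary laboratory outcome is often left to the analysis plan, which is not shown. The gain is also small beside what the trial can already detect: about 0.13 g/dL under the assumptions above, against the 0.6 g/dL (9.9 against 9.3) reported in the earlier vaginal-delivery trial.

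Most of this stands and sets the low priority. Two things remain. The article does name its tests for continuous outcomes, so the comment is on a stated method and not on an omission. And the 0.6 g/dL came from a trial in which PPH fell from 6.8 % to 1.8 %, a relative reduction of about 74 %. This trial plans for 30 %, so a smaller hemoglobin difference is plausible.

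Some stronger readings are tempting but are not supported:

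- **Bias from regression to the mean.** Randomization makes it equal in expectation in both arms, so it does not bias the contrast.
- **Subtraction merely adds the baseline's noise.** It also removes stable differences between women. With equal SDs the change has 2(1 − r) times the variance of D2 alone: 1.4 times at r = 0.3, but 0.6 times at r = 0.7.
- **The relative-risk sentence leaves continuous outcomes with no effect measure.** The outcomes are defined as means, so a mean difference is implied. The sentence is loose condensation.
- **Kruskal-Wallis replaces the stated mean.** The protocol uses it only where needed. With about 1800 women per arm, analysis of variance would ordinarily do.

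**Conclusion.** The point holds as a modest loss of precision on two secondary outcomes. The algebra is certain: in large samples ANCOVA is never less precise than the raw change. The size of the gain is not certain. The 3 % to 35 % range rests on an assumed correlation of 0.3 to 0.7 and an assumed SD ratio of 1.0 to 1.2. Letting the ratio run from 0.8 to 1.25 at the same correlations widens the saving to 2 % to 50 %.

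A reader might infer from the middle case (r = 0.5, equal SDs, ratio 0.75) that the trial forgoes the equivalent of one third more women. That is 1/0.75 at one assumed point and should not be quoted as the loss. Nor do the documents show that a hemoglobin difference that matters would be missed. Validity, the primary outcome and the sample size are untouched.

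**What to change.** State that D2 hemoglobin and hematocrit (with the existing D3 and D1 fallback) will each be analysed by a linear model with arm, pre-delivery value and center, reporting the adjusted mean difference with its 95 % confidence interval. Limit the relative-risk sentence to binary outcomes. Keep the rank test as a sensitivity analysis.

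The cost is wording only. The pre-delivery value is already required to compute the change, so no woman who could enter the planned comparison is lost. It also precedes the study drug, which is given after birth. If the analysis plan already specifies such a model, the sponsor need only confirm it.

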#### Clinical

Hemodynamic parameters (heart rate, blood pressure) 15, 30, 45, 60 and 120 min after delivery.the occurrence of potential mild adverse effects of TXA in the delivery room:■ nausea■ vomiting■ phosphenes■ dizzinessthe occurrence of potential severe adverse effects of TXA up to three months of postpartum:■ deep vein thrombosis, if the diagnosis is confirmed by Doppler ultrasound■ pulmonary embolism, if the diagnosis is confirmed by radiological examinations.■ myocardial infarction■ seizure■ renal failure needing dialysis■ any other unexpected adverse events.

These events will be checked by the medical team during the hospitalization and then on D90 by a telephone interview of each woman. In the event that the woman cannot be reached, at least 10 calls at different hours over the course of the week will be made to minimize loss to follow-up. In cases of severe adverse effects reported by a woman after the hospital discharge, objective data will be collected from medical files, transmitted either by the woman herself or her general practitioner.

#### Laboratory

urea and creatinemia, prothrombin time (PT), active prothrombin time (aPTT), aspartate and alanine transaminase, and total bilirubin at D2Women’s satisfaction and psychological statusThese will be assessed by a self-administered questionnaire on day 2 postpartum and by mail on day 60.

### Statistical analysis

Data analysis and reporting will follow the CONSORT guidelines for randomized controlled trials and will be conducted with the trial statistician and researchers blinded to group status. The two groups will be compared for women’s demographic characteristics and standard risk factors for PPH. Then we will seek, in an intention-to-treat analysis, the existence of a “TXA effect”, that is, a difference between the two groups for the primary outcome measure and the secondary outcome measures. For secondary outcomes that are available for women who had a cesarean delivery after randomization (percentage of women requiring supplementary uterotonic agents, mean change in peripartum hemoglobin, mean change in peripartum hematocrit, incidence of postpartum transfusion, arterial embolization, and emergency surgery), a secondary analysis will be conducted that includes these women. The comparisons will use nonparametric statistical tests when required by the constraints of population size or distributions. Comparisons of the categorical variables will use chi2 and Fisher exact tests, as appropriate. We will use analysis of variance and Kruskal and Wallis’s nonparametric test for the continuous variables. Effects will be measured as relative risks, with their 95 % confidence intervals.

The analysis plan includes an intermediate statistical analysis when half of the planned women have been included to ensure there is no significant difference in the adverse events between the two groups.

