### Sample size

In the recent RCT (TRACOR trial), involving the same participating centers, mentioned above, comparison of the efficacy of the controlled cord traction and standard placenta expulsion in preventing PPH showed that the PPH rate (measured postpartum blood loss of 500 mL or more) was 10.0 % (402/4013), with no significant heterogeneity between centers [14].

Accordingly, for this study, we assumed a 10 % incidence of PPH in the absence of TXA. To show a relative reduction of at least 30 % in this incidence in the TXA arm—that is, an incidence of 7 % or less in this arm, with a = 0.05, 1-ß = 0.90, and a bilateral test, the study requires 1814 women with vaginal deliveries in each group. Given the expected proportion of women with a cesarean delivery in labor after randomization (estimated at 5 % to 10 % [6.8 % in the TRACOR trial] [14]), the total number of randomized women will be greater in order to include the needed number of women with vaginal deliveries: 2000 women will be included in each group, for a total of 4000 participants.

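### Randomization is stratified by center, but the tests the article names take no account of center: a small, conservative loss of precision that costs nothing to remove

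*Protocol article*

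**What the plan says.** The randomization paragraph, which closes the Exclusion criteria section of the protocol article, says: "The randomization will be centralized and stratified by center and balanced in blocks of variable sizes".

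The Statistical analysis section then names its methods:

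- Categorical outcomes, including the primary: "Comparisons of the categorical variables will use chi2 and Fisher exact tests, as appropriate".
- Continuous outcomes: "We will use analysis of variance and Kruskal and Wallis’s nonparametric test for the continuous variables".
- Effect measure: "Effects will be measured as relative risks, with their 95 % confidence intervals".

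No stratified test, center factor or adjusted model is mentioned.

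The Sample size section bears on how much this matters. It reports that the earlier cord-traction trial had a PPH rate of 10.0 % (402/4013), "with no significant heterogeneity between centers".

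**The concern.** Stratified allocation balances the arms within each center, so differences between centers largely cancel out of the treatment comparison. A pooled test estimates its standard error from all women together, and that estimate still contains the between-center variation. If centers differ, the reported standard error is larger than the true one. Confidence intervals are then wider than they need to be, the real type I error falls below 5 %, and some power is lost.

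The article goes beyond leaving the point open, because it names the tests. Chi-square, Fisher and Kruskal-Wallis, as named, have no place for a stratification factor. Analysis of variance could carry one, but none is stated. At stake is a little precision, and agreement between how the trial allocates and how it analyses.

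**Working it through.** **1. The plan's own figure.** Inputs from the Sample size section: "we assumed a 10 % incidence of PPH in the absence of TXA"; for TXA "an incidence of 7 % or less in this arm"; α = 0.05; "1-ß = 0.90, and a bilateral test". The unstratified pooled two-proportion formula is

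n = [z₀.₉₇₅·√(2p̄(1−p̄)) + z₀.₉₀·√(p₀(1−p₀) + p₁(1−p₁))]² / (p₀−p₁)²

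With p₀ = 0.10, p₁ = 0.07, p̄ = 0.085:

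n = [1.960·√0.15555 + 1.282·√0.1551]² / 0.03² = (0.7730 + 0.5047)² / 0.0009 = 1813.95, so 1814 per group.

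This is exactly the stated number. The sample size was built for an unstratified comparison and agrees with the named test.

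**2. How center variation enters.** Write ICC = (between-center variance) / [p(1−p)] for a binary outcome. Then

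- pooled SE / true SE = 1/√(1−ICC)
- actual α = 2·[1 − Φ(1.96/√(1−ICC))]

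**3. Primary outcome: what the heterogeneity statement implies.** The article does not give the number of centers, so 15 is assumed, about 4013/15 = 267.5 women each. A 5 % heterogeneity test on 14 degrees of freedom is non-significant below 23.68, a ratio of 23.68/14 = 1.692. The largest moment estimate compatible with that is

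ICC = (1.692 − 1) / (1.692 − 1 + 267.5) = 0.0026

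With 5 centers assumed it is 0.0017, with 20 it is 0.0029. Hence the bound of about 0.003.

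- ICC 0.002: SE 0.10 % too large, actual α 0.0498.
- ICC 0.003: SE 0.15 % too large, actual α 0.0497.

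For scale, ICC 0.01 around a 10 % rate already means a between-center SD of √(0.01 × 0.09) = 3 points. In simulated heterogeneity tests on 4013 women (5 to 20 centers assumed), that ICC gave a significant result in 88 % to 95 % of runs.

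**4. Primary outcome: simulation over a wider range.** Assumed: 15 equal centers, about 1814 women per arm, 10 % against 7 %, 40,000 runs per setting.

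| Between-center SD (points) | Center rates, control | SE too large (formula) | Type I error, pooled / stratified | Power, pooled / stratified |
|---|---|---|---|---|
| 0 | 10 % | 0 | 0.050 / 0.050 | 90.2 % / 90.2 % |
| 1 | 8.2–11.9 % | 0.05 % | 0.050 / 0.050 | 90.2 % / 90.2 % |
| 2 | 6.6–13.9 % | 0.2 % | 0.048 / 0.048 | 90.3 % / 90.3 % |
| 3 | 5.2–16.1 % | 0.5 % | 0.049 / 0.050 | 90.4 % / 90.6 % |
| 5 | 2.8–20.9 % | 1.3 % | 0.049 / 0.052 | 90.4 % / 90.8 % |

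The SE column uses the variance of the 15 simulated center rates. The Monte Carlo standard error of a type I error is √(0.05 × 0.95/40,000) = 0.0011, so those differences are close to noise.

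**5. Continuous outcomes.** The article gives no center variation for measured blood loss or for hemoglobin and hematocrit change. The ICC values below are assumptions, put through the formulas of step 2:

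| Assumed ICC | SE too large | Actual α |
|---|---|---|
| 0.02 | 1.0 % | 0.048 |
| 0.05 | 2.6 % | 0.044 |
| 0.10 | 5.4 % | 0.039 |

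**The case against.** The best defence is that a journal article condenses the analysis plan. It lists test families in a few sentences, and how stratification factors enter a model is usually settled in a document not shown here. Analysis of variance can include center, and the article does not say how the relative risks will be estimated. The named test and the sample size agree, and leaving center out cannot inflate false positives here. For sparse outcomes such as embolization, center strata would often be empty, and Fisher's test is sensible.

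Most of this stands. It limits the point to the tests the article names and makes it one of efficiency. It does not dispose of it: chi-square is named for categorical outcomes, the primary among them, and a better choice using data already collected is available.

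The report of no significant heterogeneity also carries weight, with two limits. A non-significant test bounds the estimated ICC, not the true one. It also concerns one binary outcome, and the Feasibility section says that most of the present centers took part in the earlier trial, whereas the Sample size section speaks of the same ones.

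A reader might infer that the primary analysis loses appreciable power, or that its type I error is nearer 4 % than 5 %. That needs an ICC of 0.05 to 0.10, a between-center SD of about 7 to 9 points around a 10 % rate, which the heterogeneity statement makes implausible. A reader might also infer that secondary outcomes certainly lose more. The article has no figure for this. Letting the attendant decide when to remove the bag, and the department how to manage PPH, makes center differences plausible but does not measure them.

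**Conclusion.** The point holds as a minor mismatch between design and named analysis. Its direction is certain whenever centers differ: standard errors slightly too large and tests slightly conservative. Neither the validity of the trial nor the 1814 per group is in question.

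For the primary outcome the effect is negligible on the article's own evidence and stays below half a point of power under much larger assumed variation. For continuous outcomes it could reach a few percent of the standard error, but only if centers differ materially. All sizes rest on an assumed number of centers and assumed ICCs. The case for changing the plan is that the improvement is free.

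**What to change.** In the Statistical analysis section, or in the analysis plan before unblinding:

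- **Primary outcome:** center-stratified Mantel-Haenszel relative risk with its 95 % confidence interval, tested with Cochran-Mantel-Haenszel.
- **Continuous outcomes** (blood loss, hemoglobin and hematocrit change): a linear model with treatment and center.
- **Rare events:** keep exact tests.
- **Sensitivity:** report the crude test for the primary outcome.

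The cost is a few lines of text. Center is the randomization stratum and so is known for every woman, and the sample size does not change. Fixing this in advance also removes a later choice between crude and stratified results.
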